## Abstract

Chronic thromboembolic pulmonary hypertension (CTEPH) is a severe but treatable disease that is commonly underdiagnosed. Computed tomography lung subtraction iodine mapping (CT-LSIM) in addition to standard CT pulmonary angiography (CTPA) may improve the evaluation of suspected chronic pulmonary embolism and improve the diagnostic pick up rate. We aim to recruit 100 patients suspected of having CTEPH and perform CT-LSIM scans in addition to the current gold standard test of nuclear medicine test (lung single photon emission computed tomography (SPECT) imaging) as a pilot study which will contribute to and inform the definitive trial. The diagnostic accuracy of CT-LSIM and lung SPECT will be compared. The primary outcome of the full definitive study is non-inferiority of CT-LSIM versus lung SPECT imaging.

## Introduction

1

Chronic thromboembolic pulmonary hypertension (CTEPH) is a treatable, life-threatening disease that occurs in up to 4% of patients following acute pulmonary embolism (PE) [1]. The disease is characterised by remodelling of the pulmonary arteries due to poor clearance of clot. Prognosis is very poor without treatment, and pulmonary endarterectomy (PEA) is well established as the definitive and potentially curative treatment method for CTEPH.

The European Society of Cardiology recommends ventilation/perfusion single photon emission tomography (V/Q SPECT) as the first line-screening test for patients with CTEPH. The perfusion image involves injection of 99mTc labelled macroaggregated human albumin, exposing the patient to ionizing radiation and the study acquisition time is 30–40 min.

Evaluation of the pulmonary arterial tree by computed tomography pulmonary angiography (CTPA) and lung perfusion is required to determine the appropriate treatment strategy in chronic thromboembolic disease (CTED). Recently, there has been much interest in the application of lung perfused blood volume images using dual-energy CT (DECT) to assess lung perfusion [2,3]. However, DECT is not widely available in hospitals across the UK and V/Q SPECT remains the reference standard. The rationale, methodology and design of the IodiNe Subtraction mapping in the diagnosis of Pulmonary chronIc thRomboEmbolic disease (INSPIRE) study are summarised in this paper.

### Rationale of the INSPIRE study

1.1

Computed tomography lung subtraction iodine mapping (CT-LSIM) and accompanying software is now available in routine clinical practice (Sure subtractionTM, Toshiba Medical Systems; FDA report K130960). CT-LSIM images are created using on a non-rigid registration of a low dose unenhanced thoracic CT to a CTPA, with both examinations performed during the same sitting in less than 10 min total scanning time. Subtraction of the non-contrast CT from the contrast-enhanced CTPA produces the CT-LSIM. CT-LSIM simultaneously provide high-spatial-resolution images of the pulmonary arterial tree and parenchymal anatomy in combination with functional examination of lung perfusion.

Magnetic resonance imaging (MRI) is an alternative approach with the advantage of the lack of ionizing radiation and can produce lung perfusion maps with good diagnostic accuracy for CTED [5]. MRI is relatively limited in comparison to CT in terms of availability and the lack of ability to provide an out of hours service in some centres. Recently, it has been shown that Gadolinium is deposited in the basal ganglia, the clinical significance of the retained gadolinium in the brain, if any, remains unknown [4]. Further research is ongoing.

A recent meta-analysis and systematic review, highlights the diagnostic potential of CT in both screening and for surgical and interventional operability [6].

Replacement of CT for V/Q SPECT in the setting of screening for CTED would lead to a £325 saving per patient. The diagnosed annual incidence of CTEPH is approximately 700 cases in the UK, projected to rise to about 1000 in 2025. Estimated pick up rate of perfusion defects in patients with suspected CTED is 59% at a specialist centre (pick up rates are likely to be much lower at non-specialist centres). An estimated 1186 patients are screened at specialist centres, if these patients were screened using CT instead of SPECT, cost savings would be made in the UK based on current estimates.

In patients found to have CTED on lung SPECT, CTPA is also required to characterise the extent of pulmonary arterial clot for surgical planning which adds further cost. The total saving of a pathway using CTPA with iodine subtraction mapping for screening and surgical planning is potentially significant.

#### Aims and objectives of the INSPIRE study

1.1.1

The main objective of the INSPIRE study is to assess the diagnostic performance of CT-LSIM for evaluation of pulmonary perfusion in patients with known or suspected CTEPH. The primary hypothesis is that CT-LSIM is more sensitive than V/Q SPECT and CTPA in the assessment of CTED in patients with known or suspected CTEPH. We also hypothesize that the diagnostic performance of the experienced observers will be better than the less experienced and that the number of alternate diagnoses made on CT-LSIM will be higher and more accurate than lung SPECT imaging.

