### Sample size

2.9

This study has been powered to demonstrate non-inferiority of CT LSIM compared to SPECT lung scintigraphy, with 90% power, assuming a percentage success estimated from a previous study, assuming 95% sensitivity and 95% specificity; a 10% non-inferiority margin and 11% discordant pairs. This proportion must be bigger than the non-inferiority margin of 10%. With 90% power and 5% two-sided significance and estimated prevalence of 60%, 290 cases are required (116 without the disease and 174 with the disease). The pilot study we will aim to recruit 100 cases which will contribute to the definitive trial. The analysis of the results of the pilot study will allow a more precise estimate of full trial size.

We perform approximately 260 SPECT lung scintigraphy scans a year for suspected CTED/CTEPH and we expect to recruit 50% of these patients based on studies on CTED/CTEPH patients previously done at our institution. Hence would expect to complete the pilot study recruitment (n = 100) in 1 year and the full study in approximately 3 years depending on recruitment rate and sensitivity/specificity results from the pilot study. A flow chart of study design is shown in Fig. 3.

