### Statistical analysis

2.10

A Statistical Package for the Social Sciences Program (SPSS) version 24 for Windows (SPSS Inc. Chicago, IL) will be used for statistical analysis. Continuous variables will be expressed as mean ± standard deviation (SD) for parametric variables and median (interquartile range) for non-parametric variables. Categorical data will be presented as the number of subjects and percentage.

A Chi-squared test will be used to establish sensitivity, specificity, positive and negative predictive values for detecting the presence and absence of PE. The Kappa (*κ*) statistic will be used to determine the level of agreement between the independent observers. The *κ* value will be defined as follows: values < 0 indicated lack of agreement; 0–0.20, slight agreement; 0.21–0.40, fair agreement; 0.41–0.60, moderate agreement; 0.61–0.80, substantial agreement; 0.81–1, almost perfect agreement.

All statistical tests will be two sided with a p value of less than 0.05 considered to be statistically significant.

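### The primary hypothesis claims superiority in sensitivity over SPECT and CTPA, but the primary outcome and the 290-patient sample size are for non-inferiority to SPECT alone, so the stated 90% power does not apply to it

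*Protocol article*

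**What the plan says.** Three statements in the protocol article define what is primary.

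- Section 1.1.1 (Aims and objectives): "The primary hypothesis is that CT-LSIM is more sensitive than V/Q SPECT and CTPA in the assessment of CTED". This is superiority, on sensitivity only, against two comparators.
- Abstract: "The primary outcome of the full definitive study is non-inferiority of CT-LSIM versus lung SPECT imaging". This is non-inferiority against one comparator.
- Section 2.9 (Sample size): "This study has been powered to demonstrate non-inferiority of CT LSIM compared to SPECT lung scintigraphy, with 90% power". The inputs are "assuming 95% sensitivity and 95% specificity" and "a 10% non-inferiority margin and 11% discordant pairs", and the result is "With 90% power and 5% two-sided significance and estimated prevalence of 60%, 290 cases are required (116 without the disease and 174 with the disease".

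Section 2.10 gives only a general rule: "All statistical tests will be two sided with a p value of less than 0.05 considered to be statistically significant". No section gives a superiority effect size, an input for the CTPA comparison, or a sequence from non-inferiority to superiority.

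**The concern.** The statements differ in direction (superiority or non-inferiority), in comparators (SPECT and CTPA, or SPECT alone) and in the measure (sensitivity alone, or both sensitivity and specificity). If CT-LSIM proves as accurate as SPECT, the study succeeds by the Abstract and section 2.9 and fails by section 1.1.1. If it is slightly less sensitive but inside the margin, it meets the primary outcome while contradicting the primary hypothesis.

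With both called primary, the headline claim could be chosen once results are known. The staged design makes this more than theoretical. Of the pilot, section 2.9 says "The pilot study we will aim to recruit 100 cases which will contribute to the definitive trial", and the pilot results will also be used to refine the full trial size. A reader of the article would also take the 90% power to cover the stated primary hypothesis.

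**Working it through.** **1. Reproduce the plan's figure.** Inputs from section 2.9: discordant proportion ψ = 0.11, margin 0.10, two-sided 5% (z = 1.960), 90% power (z = 1.282), prevalence 60%. For paired non-inferiority with true difference 0:

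n = (1.960 + 1.282)² × 0.11 / 0.10² = 115.6, so 116 per disease group.

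The non-diseased group (40%) is the smaller and sets the total: 116 / 0.40 = 290, and 290 × 0.60 = 174 diseased. This matches exactly. Other choices do not: a one-sided 5% level gives 95 per group (total 238), 80% power gives 87 (total 218), and an unpaired formula gives 100 per group. An assumed 3-point advantage for CT-LSIM would give (3.242)² × (0.11 − 0.03²) / 0.13² = 67.9, so 68 per group and a total of 170. The 290 therefore rests on equal accuracy.

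**2. Power for what was sized.** Non-inferiority power is Φ(0.10 / √(0.11/n) − 1.960).

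- Specificity, n = 116: Φ(3.247 − 1.960) = 0.901.
- Sensitivity, n = 174: Φ(3.977 − 1.960) = 0.978.
- Both required, treating the two groups as independent: 0.978 × 0.901 = 0.88.

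**3. Power for superiority in sensitivity over SPECT, 174 diseased.** The article gives no effect size, so the CT-LSIM sensitivities below are assumptions, with SPECT at 95%. The test is a two-sided 5% McNemar test, counting wins for CT-LSIM. Two error patterns show the range.

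- *Independent errors.* At 98%, the discordant probabilities are 0.98 × 0.05 = 0.049 in favour of CT-LSIM and 0.02 × 0.95 = 0.019 against. At 99% they are 0.0495 and 0.0095.
- *Fully nested errors.* CT-LSIM misses only cases that SPECT also misses, so every discordant pair favours CT-LSIM. The uncorrected statistic then equals the number of such pairs and exceeds 3.84 from 4 pairs on. Power is P(Bin(174, 0.03) ≥ 4) = 0.77 at 98% and P(Bin(174, 0.04) ≥ 4) = 0.92 at 99%.

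| CT-LSIM sensitivity | Independent, uncorrected (exact test) | Nested, uncorrected (exact test) |
|---|---|---|
| 95% (plan's assumption) | 2.5% (1.4%) | not applicable |
| 98% | 31% (23%) | 77% (42%) |
| 99% | 60% (49%) | 92% (70%) |

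At the plan's 11% discordance, a 3-point gain has power Φ((0.03√174 − 1.960√0.11) / √(0.11 − 0.03²)) = Φ((0.396 − 0.650) / 0.330) = 0.22. This uses the plan's figure as given, although with both sensitivities at 95% discordance among the diseased cannot exceed 5% + 5% = 10%.

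**4. Pilot.** At 60% prevalence, 100 patients give about 60 diseased. With independent errors and the uncorrected test, power is about 12% at 98% and 21% at 99%.

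**5. CTPA.** No input is given, so power cannot be computed from the article. For illustration only, with CT-LSIM at 95%, independent errors and 174 diseased, it runs from about 44% if CTPA is 90% sensitive to about 99% if it is 80%.

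**The case against.** The strongest defence is that the Abstract and section 2.9, the two operative statements, agree with each other. Together they name the outcome, margin, significance level, power and number. The outlier is one sentence of aims. Sizing for non-inferiority at zero difference is the usual convention and does not stop investigators hoping for superiority. Testing superiority after non-inferiority costs no type I error. This is fair, and it limits the point to a contradiction about which claim is primary. It does not remove it: section 1.1.1 calls superiority the primary hypothesis, and the article sets out no sequence that would join the two.

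A reader might also infer more than the document supports:

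- *That superiority has essentially no power.* The 2.5% at equal accuracy is just the type I error, and no sample size would raise it. For real gains, power at 174 diseased ranges from modest to high, as the table shows. For CTPA, which the Discussion describes as less sensitive than SPECT for peripheral defects, it could be high.
- *That the plan assumes its own hypothesis false.* The zero difference is a sizing convention, inferred from the single 95%/95% statement and the reproduced arithmetic. It is not stated as a belief.
- *That there is no success criterion at all.* There is one for non-inferiority. The trouble is that a second, different claim is also labelled primary.

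**Conclusion.** The contradiction stands and is in current text. The sample size arithmetic is right for non-inferiority to SPECT; it answers a different question from the stated primary hypothesis. The 90% power does not carry over to that hypothesis.

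For superiority over SPECT with 174 diseased and SPECT at 95%, power is about 31% to 77% for a 3-point gain and 60% to 92% for a 4-point gain (uncorrected McNemar, independent to fully nested errors), or about 22% for a 3-point gain at the plan's 11% discordance. An exact test gives lower figures. All of these rest on assumed gains and an assumed overlap of errors. Power against CTPA is unplanned, not shown to be low. If the hypothesis requires winning against both comparators, its power cannot exceed that against SPECT.

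**What to change.** Rewrite the primary hypothesis in section 1.1.1 to match section 2.9: CT-LSIM is non-inferior to SPECT in sensitivity and in specificity, each with a 10-point margin. State in section 2.9 that power for meeting both is about 88% on the plan's inputs if the two disease groups are independent.

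Make superiority in sensitivity over SPECT and over CTPA secondary hypotheses. State that they are not powered and are tested only after non-inferiority is shown. The CTPA test should not depend on winning against SPECT, because at equal accuracy that gate would open only about 2.5% of the time. Either test CTPA first, or test the two together with a Holm adjustment.

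The cost is wording in the protocol and any analysis plan, with no change to recruitment, imaging or reading. Superiority loses primary status, and the stated power becomes slightly less favourable. One related matter remains: the article also calls SPECT the gold or reference standard, so the reworded hypothesis should name the standard against which both tests' sensitivity and specificity are measured.

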## Materials and methods

2

### Design and setting

2.1

The INSPIRE study is a single centre cross sectional observational diagnostic study comparing the diagnostic accuracy for new test CT-LSIM with nuclear medicine SPECT. The setting of the study is a tertiary referral centre for pulmonary hypertension. Patients will be recruited during their admission to the Sheffield Pulmonary Vascular Disease unit. CT scans will be performed in the Radiology Department at the Royal Hallamshire Hospital. Patients will be identified by the Pulmonary Hypertension team from their clinic visit as suspected CTED or CTEPH. Patients will be sent information sheets and written informed consent and those will be obtained from all the patients. Consent will be taken by a research team member on admission for diagnostic visit that includes CT scanning. The study is registered on clinicaltrials.gov (NCT03806907).

### Eligibility

2.2

Patients are eligible to be included in the INSPIRE study if they are suspected to have CTED or CTEPH and require a SPECT and CTPA.

Patients will be excluded if they are less than 18 years old, unable to provide informed consent, have significant renal dysfunction (GFR <30 ml/min), have a history of hypersensitivity to contrast material or pregnant.

### Imaging protocol

2.3

Images will be evaluated for objective and subjective image quality. No additional contrast will be used as compared to standard clinical practice as patients will only undergo one CTPA scan. The CT protocol of this study has been carefully designed to have a radiation dose identical or even lower than standard CT protocols for PE detection.

### CTPA and LSIM acquisition

2.4

CT examinations will be performed on a 320 detector-row CT system (Aquilion ONE/ViSION edition; Toshiba Medical Systems, Otawara, Japan). After non-contrast CT is performed, contrast material will be injected for 25 s via an antecubital vein using a weight-adapted injection protocol. Scanning will be initiated 3 and 14 s after the attenuation in the region of interest (ROI) placed in the pulmonary artery reached the threshold of +100 HU under the single breath hold. CT images will be reconstructed using adaptive iterative dose reduction.

The image data sets shall be analyzed with the algorithm on the post-processing software attached to Aquilion ONE/Vision Edition (SURESubtraction Lung). Based on a non-rigid registration followed by subtraction of the non-contrast images from the contrast-enhanced images (CTPA images), a colour map is produced showing the iodine distribution in the lung parenchyma.

### Nuclear medicine SPECT acquisition

2.5

SPECT imaging will be performed on a General Electric Infinia SPECT system using a low energy general purpose collimator. 100 MBq 99mTc MAA will be administered through a direct intravenous injection with a needle of 21G or larger. The image acquisition parameters are: acquisition matrix 128x128, 60 projections per detector and 7 s per projection. Images will be acquired prone with the patient's arms extended above their heads, where possible.

Fig. 1 illustrates coronal (1a) and axial (1b) CT-LSIM showing a classical triangular segmental perfusion defect (red arrows). Fig. 2 illustrates coronal (2a) and axial (2b) SPECT lung perfusion scintigraphy images showing the same segmental perfusion defect. Note the sharper delineation of the perfusion defect on CT.

**Fig. 1 fig1:**
[figure not shown]
Coronal (1a) and axial (1b) CT-LSIM showing a classical triangular segmental perfusion defect (red arrows). (For interpretation of the references to colour in this figure legend, the reader is referred to the Web version of this article.)

**Fig. 2 fig2:**
[figure not shown]
Coronal (2a) and axial (2b) SPECT lung perfusion scintigraphy images showing the same segmental perfusion defect. Note the sharper delineation of the perfusion defect on CT.

### Radiation dose

2.6

The typical effective dose for lung perfusion scintigraphy, was 2.04–2.86 mSv determined by the normalized coefficient. A study of 50 patients [7] using the same scanner used in our hospital found a median dose length product of 171 mGy cm, corresponding to an effective radiation dose of approximately 2.90 mSv, using a conversion factor of 0.017 mSv/mGycm for chest CT. Hence the advantages described above can be achieved with a similar radiation dose to a nuclear medicine lung scintigraphy scan and patients who require both CTPA and SPECT have a lower total dose.

### Image analyses

2.7

All images will be anonymised and given unique study identifiers. Analysis will be performed using a commercially available diagnostic workstation (OsiriX).

### Radiological evaluation

2.8

CT-LSIM and CTPA images shall be respectively evaluated by three observers, two consultant Radiologists and a Radiology resident who were blinded to the clinical data (observer 1: a thoracic radiologist with 8 years of specialist experience, observer 2: a thoracic radiologist with 7 years of experience and observer 3 a Radiology resident with 4 years’ experience), following which a consensus read will be performed by observer 1 and 2. The scores of each reader will be adopted, as they were if scores are matched. If scores of each reader are different, either shall be adopted after the discussion of two readers. In addition, the 2nd reading session of observer 1 will be performed to determine intra-observer agreement.

LSIM images will be scored primarily as positive, negative or indeterminate. If abnormal a severity score will be assigned. Score 1, if normal perfusion, score 2 if mild perfusion defects (<25%); score 2, moderate perfusion defects (25–50%), and class 3, severe perfusion defects (>50%).

CTPA will be scored primarily as positive, negative or indeterminate. In addition, the clot burden will be semi-quantitatively scored as mild, moderate or severe, and predominantly proximal or distal.

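### The CT-LSIM severity scale puts four perfusion categories on three codes, with mild and moderate both scored 2, and codes normal scans on a scale meant for abnormal ones: a minor defect in a secondary variable

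*Protocol article*

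**What the plan says.** All the scoring rules are in the protocol article, section 2.8 (Radiological evaluation).

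- The main CT-LSIM read has three outcomes: "LSIM images will be scored primarily as positive, negative or indeterminate".
- A severity grade follows, with its trigger and first level stated together: "If abnormal a severity score will be assigned. Score 1, if normal perfusion".
- The middle levels are "score 2 if mild perfusion defects (<25%); score 2, moderate perfusion defects (25–50" per cent), and the top level is "class 3, severe perfusion defects (>50" per cent).
- The consensus rule for the two consultants is "The scores of each reader will be adopted, as they were if scores are matched"; differing scores are settled by discussion.
- Intra-observer agreement is planned: "the 2nd reading session of observer 1 will be performed to determine intra-observer agreement".

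Section 2.10 (Statistical analysis) adds that the kappa "statistic will be used to determine the level of agreement between the independent observers". It names neither the variable to which kappa applies nor any weighting. No other section gives a different severity scale.

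**The concern.** A grading scale needs one code per category and a clear rule on who is graded. This one fails on both counts. Mild and moderate defects share a code, so the 25% boundary that the protocol defines is lost in the recorded number. Whether a negative scan gets a 1 or no score depends on which half of the rule the reader follows.

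Three things are at stake: the only graded measure of CT-LSIM perfusion in the article, the rule that decides which scans the consultants discuss, and any agreement statistic computed on severity. The 100 pilot cases are to be carried into the definitive study (section 2.9), so a coding fault in the pilot would be carried with them.

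**Working it through.** **1. Categories against codes.** The last two columns show two natural repairs.

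| Category | As printed | 1–4 scale | 0–3 scale |
|---|---|---|---|
| Normal | 1 | 1 | 0 |
| Mild, <25% | 2 | 2 | 1 |
| Moderate, 25–50% | 2 | 3 | 2 |
| Severe, >50% | 3 | 4 | 3 |

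As printed there are four categories and three distinct values. The printed normal and mild codes fit the 1–4 repair; the moderate and severe codes fit the 0–3 repair. The text does not show which was meant, and the choice matters: codes 1, 2, 3 mean normal, mild, moderate on one scale and mild, moderate, severe on the other.

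**2. Does the sample size depend on this?** Section 2.9 assumes "a 10% non-inferiority margin and 11% discordant pairs", 90% power, 5% two-sided significance and 60% prevalence. The paired non-inferiority formula gives n = (1.960 + 1.282)² × 0.11 / 0.10² = 115.6, so 116 in the smaller, disease-free group. Then 116 / 0.40 = 290, and 290 × 0.60 = 174 with disease. The plan's figures reproduce exactly, and the severity scale does not enter.

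**3. Size of the effect on severity agreement.** The documents give no figure, so this is an illustration. The 60% abnormal share is the prevalence in section 2.9. The rest is assumed: each reader independently assigns the true grade with probability a = 0.7, 0.8 or 0.9 and otherwise an adjacent grade; abnormal scans split mild/moderate/severe as 33/33/33, 50/30/20 or 20/30/50.

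*Worked example, equal split, a = 0.8.* True shares are 0.40, 0.20, 0.20, 0.20. Each reader's marginal shares are 0.34, 0.26, 0.22, 0.18.

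- Four distinct levels: observed agreement 0.672; chance agreement 0.34² + 0.26² + 0.22² + 0.18² = 0.264; kappa = (0.672 − 0.264) / (1 − 0.264) = 0.554.
- Printed coding: scans split mild/moderate between the readers are a(1 − a) × (mild + moderate share) = 0.8 × 0.2 × 0.40 = 0.064. Observed agreement becomes 0.736, but chance agreement also rises, to 0.34² + 0.48² + 0.18² = 0.378. Kappa = (0.736 − 0.378) / (1 − 0.378) = 0.575.
- Linear-weighted kappa falls from 0.725 to 0.645. With four levels, a one-step disagreement earns credit 1 − 1/3 = 2/3; with three levels it earns only 1 − 1/2 = 1/2.

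*Across all nine combinations*

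| Split, a | Unweighted, 4 levels → printed | Linear-weighted, 4 levels → printed |
|---|---|---|
| 33/33/33, 0.7 | 0.407 → 0.414 | 0.617 → 0.501 |
| 33/33/33, 0.8 | 0.554 → 0.575 | 0.725 → 0.645 |
| 33/33/33, 0.9 | 0.751 → 0.769 | 0.853 → 0.811 |
| 50/30/20, 0.7 | 0.380 → 0.396 | 0.567 → 0.464 |
| 50/30/20, 0.8 | 0.536 → 0.562 | 0.688 → 0.615 |
| 50/30/20, 0.9 | 0.742 → 0.763 | 0.832 → 0.794 |
| 20/30/50, 0.7 | 0.420 → 0.420 | 0.650 → 0.525 |
| 20/30/50, 0.8 | 0.559 → 0.576 | 0.749 → 0.664 |
| 20/30/50, 0.9 | 0.749 → 0.767 | 0.866 → 0.822 |

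Unweighted kappa changes by 0.00 to +0.03 and linear-weighted kappa by about -0.04 to -0.13.

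**4. Consensus.** The same expression gives the share of scans that would be matched only because of the shared code. The lowest value is 0.9 × 0.1 × (0.60 × 0.50) = 0.027 and the highest is 0.7 × 0.3 × (0.60 × 0.80) = 0.101. That is about 3% to 10% of all scans under these assumptions.

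**The case against.** The best defence is that this is a numbering slip in a condensed article. Each category has its own label and percentage band; only the numeral repeats, and the switch from score to class at the last level points to an editing error. The reading form is not shown and may be correct. Section 2.10 does not say that kappa is applied to severity. If it is applied to the positive/negative/indeterminate read, the severity codes cannot affect it. A mild and a moderate read are both abnormal, so a skipped discussion leaves sensitivity and specificity untouched.

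Most of this stands, and it limits the point to a secondary variable. It does not remove the point: the sentence is an operative scoring rule, nothing else in the article corrects it, and the two obvious repairs give the same numerals different meanings.

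Two stronger readings are tempting, and the documents support neither. A reader might infer that the coding inflates observer agreement. Raw percentage agreement on severity would rise by exactly the share of mild/moderate splits, but the article plans kappa, does not tie it to severity, and the direction depends on the weighting. A reader might also infer that the severity data are irrecoverable. That follows only if the form stores the bare numeral without the category or the extent.

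**Conclusion.** The defect is certain as a matter of text: four categories have three codes, and normal perfusion has a code on a scale reserved for abnormal scans. Followed literally, the score loses the 25% cut and lets mild/moderate splits between the consultants pass as matched. The consensus consequence assumes that the matching rule covers the severity score, which its wording does not exclude. Any effect on kappa is conditional on kappa being computed on severity and is modest at the assumed reader accuracies and severity splits. Nothing in the main read, the CT-LSIM versus SPECT accuracy comparison or the sample size changes. This is a minor defect, worth correcting because the rule is wrong as written and the correction is nearly free.

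**What to change.** In section 2.8, give each perfusion category one distinct code. Either 0 normal, 1 mild, 2 moderate, 3 severe, or 1 to 4 in the same order, would do; the investigators should say which they meant. State whether negative scans receive a severity score, and whether indeterminate scans do. Align the reading form with the corrected text before reading starts.

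If agreement on severity is to be reported, compute it on the corrected distinct levels. Weighted kappa is an option for an ordinal grade, not a necessary correction.

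The cost is a one-line change to the text and a check of the form. Scans already scored can be re-coded from the recorded category or extent; only those for which the numeral alone was kept would need a re-read.
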